##### Statistical analysis

This hypothesis is tested in two separate bivariate analysis - one comparing the multilevel intervention group (E+I) to the environment intervention only group (E) and the other comparing the multilevel intervention group (E+I) to the individual level intervention only group (I).

Hypothesis 3: Participants living in developments receiving the combined intervention (E+I) will demonstrate even greater increases in the number of minutes of moderate intensity physical activity per week (individual level) and the proportion meeting the recommended physical activity guidelines (development level) from baseline to 24-month follow-up, compared to the sum of average change in environmental intervention compared to control and the individual level intervention compared to control (synergistic effect).

##### Statistical analysis

To examine this hypothesis, we exploit our study design which has a multifactorial design embedded in a cluster randomized controlled trial. Multifactorial experimental designs combine the rigor of experimental design with the ability to produce results on the effectiveness of alternate approaches to multicomponent interventions in a single experiment. We will use multilevel regression analysis and test for an interaction effect between the environmental and individual level interventions (E+I). The presence of a significant interaction between E and I on the primary outcome of physical activity suggests synergy between these components of the intervention. If the effects of the environmental level intervention and individual level intervention are additive there should not be a significant interaction in the model. In this case, we can compare the interaction results to the multilevel intervention group (E+I) to examine the exploratory hypothesis that E+I is more effective than E&I combined.

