##### Between group analysis

The between group hypothesis is tested in three separate bivariate analyses comparing each intervention group to the control group in two primary outcomes based on the cluster-randomized design. We examine change in each primary outcome pre-intervention to post-intervention: 1) the number of minutes of moderate or greater intensity physical activity per week (continuous); and 2) meeting the recommended guidelines of >150 minutes of moderate or greater intensity physical activity per week (dichotomous at individual level, proportion at group level). In addition, we will examine this hypothesis controlling for potential confounding factors and any variables that violate the randomization assumption using multilevel multivariable linear (continuous outcomes) and logistic (binary outcomes) regression models.

Hypothesis 2: Participants living in developments receiving the combined intervention (E+I) will demonstrate even greater increases in the number of minutes of moderate intensity physical activity per week (individual level) and the proportion meeting the recommended physical activity guidelines (development level) from baseline to 24-month follow-up, compared to either intervention delivered singly.

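### The Hypothesis 3 rule sets no sign for synergy, leaves no room for an inconclusive result, and appears to re-ask the same question on the additive branch

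*Protocol article*

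**What the plan says.** All references are to the Protocol article, Analysis plan, Aim 1, unless stated.

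- **The hypothesis.** Hypothesis 3 (stated at the end of the Statistical analysis text for Hypothesis 2) says that residents of E+I developments will show greater increases "compared to the sum of average change in environmental intervention compared to control" plus the corresponding change for I. It covers minutes of activity and "the proportion meeting the recommended physical activity guidelines (development level) from baseline to 24-month follow-up, compared to the sum of average change".
- **The test.** The Statistical analysis text for Hypothesis 3 calls for a multilevel regression with an E by I interaction. It names no link function and no direction of test.
- **The reading of the result.** "The presence of a significant interaction between E and I on the primary outcome of physical activity suggests synergy between these components". The next sentence adds: "If the effects of the environmental level intervention and individual level intervention are additive there should not be a significant interaction in the model".
- **The follow-on step.** The last sentence of that paragraph refers back to the case just described. It proposes to compare the interaction results with the E+I arm, to explore whether E+I does better than E and I put together.
- **The model for binary outcomes.** Under Between group analysis, for Hypothesis 1, the adjusted analysis uses "multilevel multivariable linear (continuous outcomes) and logistic (binary outcomes) regression models".
- **Power.** Aim 1 - between group analysis sample size gives more than 90% power for a 5-minute (or 5 percent) difference between two groups, with 3 clusters of 32 per group. It gives no SD or intracluster correlation (ICC). No power is given for Hypothesis 3.

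**The concern.** The hypothesis and the rule that is meant to test it do not ask the same question. The hypothesis is met only by a positive departure from additivity. The rule, as worded, is met by a departure in either direction.

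The two sentences on interpretation name a significant result (synergy) and the additive case (no significant interaction). They leave no place for a result too imprecise to tell. The closing sentence then appears to reopen super-additivity on the second branch. That would be the same contrast again, after its test was null.

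Hypothesis 3 sits under the primary aim. Followed literally, the rule could count antagonism as support for combining the components, or draw a second conclusion from a contrast that has just been tested.

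**Working it through.** **1. Contrast against rule.** Write each term as an arm's mean change. Hypothesis 3 says (E+I − C) > (E − C) + (I − C), which rearranges to

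D = (E+I) − E − I + C > 0.

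In a linear model with E and I coded 0/1, the E by I coefficient is D. For minutes, the test and the hypothesis therefore share a scale and differ only in sign. Example: E alone gains 5 minutes over control, I alone gains 5, and E+I also gains only 5. Then D = 5 − 5 − 5 + 0 = −5. A two-sided test detects −5 as often as +5, and a significant result would meet the rule although Hypothesis 3 is false.

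**2. Precision.** The variance of an arm mean is V = SD²[1 + (m − 1)ICC]/(mk), with m = 32 and k = 3. A pairwise contrast has variance 2V and D has 4V. The SE ratio is √2 with equal arms, whatever the SD and ICC.

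The plan's figure of more than 90% cannot be reproduced without an SD and ICC. A scan over assumed values (normal approximation, two-sided 0.05, difference of 5 minutes) gives:

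| SD | ICC | Pairwise power | Interaction power |
|---|---|---|---|
| 4 | 0.05 | >99% | 97% |
| 8 | 0.02 | 92% | 67% |
| 10 | 0.02 | 78% | 49% |

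Only the first two rows agree with the plan's statement.

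Now suppose that pairwise power at 5 minutes is exactly 90%:

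- Pairwise SE = 5/(1.960 + 1.282) = 1.542; SE of D = 1.542 × 1.414 = 2.181.
- Power for D = 5: Φ(5/2.181 − 1.96) = Φ(0.332) = 63%.
- Power for D = 2.5: Φ(1.146 − 1.96) = 21%.
- 90% power needs D = 3.2415 × 2.181 = 7.1 minutes.
- 95% CI half-width = 1.96 × 2.181 = 4.3 minutes.

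With t reference distributions instead (4 df pairwise, 8 df for the interaction), again set to 90% pairwise power, the power for D = 5 is 78% and the half-width is 3.7 minutes.

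**3. Scale for the guideline outcome, if logistic regression is used.** With no logistic interaction, the odds in E+I equal odds(E) × odds(I)/odds(C). Assume that E and I each add 10 percentage points. The control rates are also assumed. The only related figure in the document is that about 62% of residents report insufficient activity (Participants), which leaves about 38%; this is not an accelerometer rate in the cohort.

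| Control | E+I if additive | E+I if no logistic interaction | Gap (points) | Interaction odds ratio if exactly additive |
|---|---|---|---|---|
| 5% | 25% | 37.2% | 12.2 | 0.56 |
| 10% | 30% | 36.0% | 6.0 | 0.76 |
| 20% | 40% | 42.4% | 2.4 | 0.91 |
| 38% | 58% | 58.2% | 0.2 | 0.99 |

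Row 2 in full: odds are 0.25 × 0.25/0.1111 = 0.5625, so the E+I rate is 0.5625/1.5625 = 36.0%. At a 10% control rate, an E+I rate between 30% and 36% would be synergy under Hypothesis 3 but would have a negative logistic coefficient.

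**The case against.** **On sign.** The analysis text is introduced as a test of Hypothesis 3, which is plainly directional, and it says only that a significant interaction suggests synergy. A sensible analyst would look at the sign. This stands as a reason not to rate the point highly. It does not repair the rule: neither a sign nor a one-sided test is stated.

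**On additivity.** A reader might infer that the plan declares additivity whenever the interaction is not significant, so that a true 5-minute synergy would be called additive 37% of the time (100 − 63). The document does not support this. It states the converse: if effects are additive, no significant interaction is expected. The 37% also needs pairwise power of exactly 90%, where the plan claims more than that and gives no SD or ICC. The √2 ratio itself belongs to every 2×2 interaction contrast and is not an error. What remains is that no inconclusive outcome is provided for.

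**On the last sentence.** Its back-reference and its comparison are unclear, and the plan labels the step exploratory. Re-asking the same contrast is the natural reading but not the only one.

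**On scale.** A reader might infer that the plan will test the guideline outcome on the wrong scale. That is not established. The Hypothesis 3 text names no link; logistic models are named only under Hypothesis 1; and a development-level proportion can be modelled linearly. The size is also limited. In the 10/20/20/30% example with 96 per arm, the SE of D before clustering is √[(0.09 + 0.16 + 0.16 + 0.21)/96] = 8.0 points, so the 6-point gap is less than one SE. It biases the estimand more than it would by itself produce a false significant result.

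**Conclusion.** The point holds at moderate severity. Two parts rest on the text alone: the rule has no sign condition although the hypothesis is directional, and the closing sentence appears to put the same super-additivity question again on the additive, non-significant branch.

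The absence of an inconclusive category matters because the contrast has twice the pairwise variance and no stated power. The only power figure for an interaction among group means, under LMS method, is for Aim 2 moderation. The 63% (78% with t distributions) is an illustration conditional on 90% pairwise power, not a property of the trial.

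The scale mismatch is conditional on carrying the logistic model over from Hypothesis 1. Its size depends on the cohort's guideline rate, which is not given: 6 to 12 points at control rates of 10% and 5% with 10-point effects, and 0.2 points at 38%. The minutes outcome is unaffected, as are the pairwise comparisons of Hypotheses 1 and 2.

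**What to change.** 1. Define the Hypothesis 3 contrast as (E+I) − E − I + control on the additive scale: minutes for the continuous outcome and percentage points for the guideline outcome. If a logistic model is used for the latter, obtain the contrast by marginal standardisation; otherwise use cluster-level proportions.
2. Report the contrast with its 95% CI. Claim synergy only if the interval lies above 0 and sub-additivity only if it lies below 0. Report any other result as inconclusive, with the interval.
3. Delete the last sentence of the Hypothesis 3 analysis text, or rewrite it as a distinct comparison with its own definition.

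The cost is wording and, for the guideline outcome, one standardisation step if a logistic model is kept. Randomisation and data collection do not change. The downside is that the trial cannot declare additivity from a non-significant test.

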#### Aim 2: mediation/moderation

We will evaluate the mediator effects of motivation, self-efficacy, neighborhood walkability, support from HLAs, and fidelity and moderator effects (i.e., sleep, financial strain, public housing development characteristics, neighborhood social cohesion, and access to physical activity resources) on physical activity behavior.

##### Statistical analysis

Mediation and moderation are examined using variables at both levels, as such we will use multilevel structural equation models and path analysis to examine multilevel mediation and multilevel moderation within and across levels [70, 71]. The multilevel structural equation model framework is flexible and allows for testing models with predictors, mediators, and outcomes on either of the two levels. Given the small number of clusters both the Random Coefficient Prediction (RCP) method and the Latent Moderated Structural Equation (LMS) method with residual bootstrapping to estimate confidence intervals will be used to examine potential moderation. In RCP a random slope is predicted by a moderator. LMS can be applied to multilevel data by creating latent interactions among random coefficients.

##### Handling missing data

While the mechanism giving rise to the missing data cannot be determined by the observations, the sensitivity of parameter estimates to missing data assumptions can be studied by fitting multiple models that make different assumptions about the missing data process  [72]. For the missing data sensitivity analysis, we will compare three missing data approaches: 1) complete case analysis, 2) multiple imputation to estimate missing data values, and 3) mixed-effects pattern-mixture model that incorporates information about patterns of missing data, such as patterns of participant dropout. In the mixed-effects pattern-mixture model, participants are grouped according to the dropout patterns, and grouping indicators are included in the model similar to other person-level covariates. The model allows for the study of how responses vary by pattern and for generating an average profile that is weighted according to the missing data patterns.

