#### Recruitment and screening of the evaluation cohort

We propose to recruit 50 participants per development in the evaluation cohort. Eligibility criteria include being able to speak English or Spanish, being 18 years old or older, being a public housing resident from one of our study sites, not planning to move within the next 2 years, having access to a phone, not currently participating in another physical activity study, being able to walk independently without regular need for special equipment (wheelchair, scooter, or walker), ability to provide informed consent, and willingness to complete the accelerometer-based device measurement. By design, the entire cohort will be low-income.

Recruitment will take place at the developments, using common sampling rules and a direct household door-knocking approach [39–41]. Trained Research Assistants will approach units based on an assigned list and will attempt to identify an eligible resident using a brief script. The survey steps will be as follows: approach the unit, attempt to identify a resident, describe the study, determine eligibility, collect informed consent documents, collect the survey measurements, explain the physical activity device, and remind the residents of follow-up visits. Data collection documents for screening, documenting informed consent, and baseline, 12- and 24-month assessments are stored in REDCap [42].

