#### Aim 1 - between group analysis sample size

We power the multivariable analysis based on test for two means in a 2-level hierarchal design with level 2 randomization. Sample sizes of 96 subjects in each group, which were obtained by sampling 3 clusters with an average of 32 subjects per cluster, achieve >90% power to detect a difference between the group means of at least 5 minutes (or 5 percent difference in meeting recommended levels). A test based on a mixed-model analysis at a significance level of 0.05.

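### The Aim 1 change tests use only residents with valid device data at both baseline and 24 months, and every method that addresses dropout is a sensitivity analysis with none named to decide

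*Protocol article*

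**What the plan says.** All references are to the protocol article.

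- **Between group analysis (Aim 1).** Hypothesis 1 is tested in three bivariate comparisons with control. The outcome is a change: "We examine change in each primary outcome pre-intervention to post-intervention". The hypothesis sets the endpoint at 24 months. Multilevel linear and logistic models are added to control for confounders and imbalance. The text does not say whether they take change scores or all visits.
- **Within group analysis.** The tests are paired (t, Wilcoxon signed-rank, McNemar).
- **Handling missing data.** "For the missing data sensitivity analysis, we will compare three missing data approaches: 1) complete case analysis", followed by multiple imputation and a mixed-effects pattern-mixture model. None is named as the analysis that gives the Aim 1 result, and nothing is said about what follows if they disagree.
- **Aim 1 between-group sample size.** "We power the multivariable analysis based on test for two means in a 2-level hierarchal design with level 2 randomization". The size is given as "Sample sizes of 96 subjects in each group, which were obtained by sampling 3 clusters with an average of 32 subjects per cluster", for more than 90% power at a difference of 5 minutes.
- **Recruitment.** "We propose to recruit 50 participants per development in the evaluation cohort".
- **Design section and Table 1.** The cohort also wears the device at 12 months.
- **Primary outcome measurement.** A valid record needs 10 waking hours a day on at least 4 days, so a value can be missing without withdrawal.

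**The concern.** A change score needs both of its values. A resident with valid baseline and 12-month records but no valid 24-month record contributes nothing to the bivariate or paired tests. Complete case, listed as the first sensitivity approach, therefore only repeats what those tests already do. The two approaches that can address selective dropout sit below them, and none has priority.

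The completer comparison is unbiased if dropout is unrelated to the course of activity, or related to it in the same way in all arms. The second condition is not assured here. Community health workers are active in every intervention development, while control developments have assessment only. If residents whose activity has fallen by 12 months leave more readily in an active arm, that arm's completers look better than its cohort. The data that would reveal this are already collected. A secondary risk is that, with no method named as deciding, emphasis could shift to one of them after the results are known.

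**Working it through.** **1. The plan's own figures.** 3 x 32 = 96 per arm reproduces. The stated power cannot be reproduced, because no SD or intracluster correlation is given; this point does not depend on it.

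**2. What the sizes would mean if read as completers.**

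| Source | Size used / recruited | Share | Implied loss |
|---|---|---|---|
| Aim 1 between-group | 32/50 | 64% | 36% |
| Moderation, RCP method | 40/50 | 80% | 20% |
| Moderation, LMS method | 41/50 | 82% | 18% |

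No passage states a dropout rate, so 18-36% is used below only as a range of scenarios.

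**3. Simulation (assumptions, not document figures).** There are 1.5 million residents per arm and no true effect. Activity is standard normal at each visit, with correlations 0.60 (baseline-12 months), 0.65 (12-24) and 0.55 (baseline-24). The SD of change is sqrt(2 x (1 - 0.55)) = 0.949 SD of activity. The same share is missing at 24 months in both arms. In the active arm, missingness is logistic in (12-month minus baseline) with slope -0.5 or -1.0. Dropout odds then rise by exp(0.5) = 1.6 or exp(1.0) = 2.7 per 1-SD fall. In control the slope is 0.

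False benefit in the active arm, in SD of change:

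| Missing at 24 months | Slope -0.5 | Slope -1.0 |
|---|---|---|
| 18-20% | about 0.05 | 0.08 to 0.09 |
| 36% | 0.09 | 0.16 |

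At 36%, for example, 0.085/0.949 = 0.09 and 0.154/0.949 = 0.16. An estimate that regresses the 24-month value on baseline and 12 months within arm, and averages over everyone with a baseline, is within about 0.001 of zero. If missingness depends on the 12-month level alone, the completer bias is 0.02 SD or less.

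**4. In minutes.** The within-group sample size (21 pairs, mean difference 3.0, 90% power, two-sided 0.05) implies an SD of change of about 4.0; SD 4 with 21 pairs gives 90.5% power. The bias at 36% missing is then 0.09 x 4 = 0.4 to 0.16 x 4 = 0.6 minutes, and at 18-20% it is 0.05 x 4 = 0.2 to 0.09 x 4 = 0.4 minutes. The figures scale with the true SD.

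**5. A check without the simulation.** With equal retention in the two arms, completer bias = (1 - retention) x gap. The gap is the between-arm difference in (completer mean change minus dropout mean change).

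| Assumed gap (minutes) | Bias at 64% retention | Bias at 82% retention |
|---|---|---|
| 2 | 0.7 | 0.4 |
| 5 | 1.8 | 0.9 |
| 10 | 3.6 | 1.8 |

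To match the whole 5-minute target the gap would have to be 5/0.36 = 13.9 minutes or 5/0.18 = 27.8 minutes. The biases of 0.36 and 0.65 minutes (0.089 x 4 and 0.162 x 4) correspond to gaps of 0.36/0.36 = 1.0 and 0.65/0.36 = 1.8 minutes, so the larger rows assume much stronger selection than step 3.

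**The case against.** Four arguments stand against the point.

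- **Missing data are addressed.** The plan names multiple imputation and a pattern-mixture model and commits to comparing all three approaches. That commitment limits selective reporting. It does not settle which estimate answers Hypothesis 1.
- **The full analysis plan may name the primary method.** This is fair for imputation detail. But the article does more than stay silent: it fixes change-based and paired tests for Aim 1 and assigns all three approaches to sensitivity analysis.
- **The powered analysis is a mixed model.** The sample-size section says so, and such a model could retain residents with partial data. A reader might infer that every Aim 1 analysis is complete-case, and the documents do not support that. It is certain only for the bivariate and paired tests. Equally, the mixed model cannot be credited with solving the problem, because its outcome form is not stated and the text just before it defines the outcome as change.
- **The bias is modest and rests on assumptions.** This stands. The correlations, the amount of loss and selection in one arm only are all assumed.

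A reader might also infer that the plan expects 32 of 50 residents to be measured at both ends, so that the main result omits about a third of the cohort. The documents do not support this. The 32 is a size sufficient for the stated power. Read the same way, the 21 pairs for the paired t-test would mean 1 - 21/150 = 86% loss per arm. The moderation sections use 40 and 41.

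**Conclusion.** The point holds for the tests as written. The Aim 1 bivariate and paired tests default to residents with valid data at both ends and leave the 12-month value unused, and no missing-data approach is set to decide. The multilevel model might avoid this but is not specified well enough to say so.

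The size is modest: a false benefit of about 0.05-0.09 SD of change at 18-20% loss and 0.09-0.16 SD at 36%. With an SD of change of 4, that is roughly 0.2 to 0.6 minutes against a target of 5. It requires dropout tied to a decline by 12 months in the active arm only. It is near zero if dropout depends only on the 12-month level. The loss range is a scenario, since the plan gives no dropout rate. The change is worth making because it is cheap and uses data already collected; the documents do not show that the trial's result would be overturned.

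**What to change.** State in the analysis plan, before 24-month data are compared by arm:

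1. The deciding 24-month comparison is a likelihood-based multilevel mixed model on the baseline, 12-month and 24-month values, with a development effect and management stratum. It keeps residents who have 12-month but no 24-month data.
2. An equivalent choice is multiple imputation that includes the 12-month device value, allows relations to differ by arm and respects clustering by development. It should not enter both development indicators and management stratum: stratum is determined by development, so the two terms are aliased, and there are only three developments per arm.
3. Complete case and pattern-mixture are sensitivity analyses that do not replace the deciding analysis.

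The cost is a short addition to the text and slightly more analysis work, with no new data. The downside is reliance on missing-at-random given the observed values, which the planned pattern-mixture analysis then probes.
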